### Environmental lighting conditions

Numerous studies have concentrated on the physiological and psychological effects of light intensity and Correlated Color Temperature (CCT, measuring how warm or cool the light appears) in older adults [23, 35, 36, 62–75]. CCT characterizes the color of light, which is based on the wavelength at which the light travels. Light that has shorter wavelengths (e.g., 450 to 530 nm) would be perceived as blue, whereas light that has longer wavelengths (e.g., 620 to 750 nm) would be perceived as red [28]. Experiencing more blue light in morning has been shown to have positive physiological and psychological effects on one’s health. Although light exists on a continuum, for the purposes of this research protocol we are defining blue light as light with wavelengths between 450 and 530 nm.

In this study, participants will experience three different lighting conditions in the kitchen and dining areas of their residences to assess how each condition affects different measures of brain health. Light bulbs originally installed in the participant’s living and kitchen areas (which emit static lighting) will be replaced by Philips Hue dynamic light bulbs (E26, warm-to-cool white, 16 W; Signify N. V.; Eindhoven, Netherlands), which can output 0 lumens to 1600 lumens (a measure of brightness of the light) and CCT from 2200 to 6500 K. Additional lamps will be installed in the kitchen and dining areas of the participants’ residences to achieve the desired brightness and color temperatures based on simulations described below. All lights used in this study are commercially available and will be installed by members of the study team.

Each lighting condition will be programmed to achieve minimum CCT and brightness levels throughout a 24-hour period (Fig. 2). The three lighting conditions that participants will experience are:

**Fig. 2 Fig2:**
[figure not shown]
24-hour schedule of lighting parameters for **a**) L1, **b**) L2, and **c**) L3 lighting conditions. L1 is designed to be a static light condition similar to what residents would typically have in their independent living residences. L2 and L3 are designed to have increased EML in the morning hours with more exposure to blue-rich light and also slightly decreased EML in the evening hours

L1: static lighting condition with fixed CCT and brightness;L2: dynamic lighting condition with dynamic CCT and brightness; and.L3: dynamic lighting condition similar to L2 but with increased brightness in the morning hours.

The light bulbs installed in each residence will be programmed and controlled using the Philips Hue Application Programming Interface (API). Each lighting condition will be implemented to achieve minimum levels of equivalent melanopic lux (EML, measured in mlux) while ensuring high levels of blue-rich light in the morning and low levels of blue-rich light in the evening. EML quantifies the circadian effect from the light source by weighting the response from ipRGCs [90, 91]. Recent studies have suggested EML is a favorable indicator of the melatonin suppression response [37, 38, 92]. A minimum EML of 280 melanopic lux (mlux) for at least 4 h during the daytime is recommended as an optimal circadian stimulus that normalizes biological responses such as melatonin suppression, circadian phase resetting, and subjective altering responses [39, 93]. As shown in Fig. 2, the L1 condition is designed to have a fixed EML throughout the 24-hour period, whereas the L2 and L3 conditions provide a cycle of gradually higher EML during the morning and lower EML in the evening. As such, the mlux values in the morning are greater in L2 and L3 compared to L1 (and less in the evening for L2 and L3 compared to L1). Guidelines provided by the WELL Building Standard were taken into consideration when selecting the EML levels for each lighting condition [93].

The purpose of the L3 condition is to increase the amount of morning EML and decrease the amount of evening EML to determine if there is a saturation effect with regards to the different measures of brain health, we are collecting in L1 and L2. Exposure to EML beyond 280 mlux may not result in any added health benefits [39]. However, older adults tend to perceive light differently than younger adults and require brighter lighting [43–47]. As such, having each participant experience the L3 condition will give us an opportunity to examine whether light intensity plays a factor in any detected changes of brain-health measures.

### Verifying lighting conditions through simulations and field measurements

To ensure the target EML and CCT values in Fig. 2 were achievable with our proposed lighting design, we conducted computer simulations and collected lighting measurements from one empty residence in the facility. Figure 3 depicts one floorplan where we identified locations where we anticipated participants will spend much of their time: (1) center of the sofa facing the living room, (2) middle of the hallway entrance facing the living room, (3) center of the pendent lights above the kitchen island facing the kitchen, and (4) underneath the light fixture in the kitchen facing the living room. We implemented our lighting intervention in this empty room while measuring the illuminance and CCT using a research grade spectrometer (CL-500 A; Konica Minolta, Inc; Tokyo, Japan) placed 1.2 m above the floor from each of these target locations to approximate the individuals seated eye-level. We set the lights to the morning scene (8:00am-12:00pm) from the L2 condition because ensuring we could achieve these target EML and CCT values confirmed we could also achieve the lower EML and CCT values as well. Using these measurements from the spectrometer, we were able to confirm that we could achieve the desired brightness levels using a 3D simulation model. This model simulated the EML values for the entire kitchen, living area, and hallway using lighting simulation software Radiance and DIVA for Rhino with proven validity. Because each residence will be slightly different in floorplan, we made certain assumptions regarding surface reflectance, melanopic ratio, and lumen adjustments for the purposes of this simulation.

**Fig. 3 Fig3:**
[figure not shown]
Drawing of an example floorplan where the lighting intervention will be implemented. Measurements are taken in four directions at specific locations in the room. Example locations and directions are shown in blue. Each floor plan has built-in lighting fixtures in the ceiling as indicated by the orange circles. Additional floor lamps will be added to the room to increase the amount of light to which participants are exposed. For the L3 condition, the amount of blue light needs to be increased compared to the L2 condition. This will be accomplished by placing a tabletop lamp in the corner above the cabinets in the kitchen. Only the kitchen and dining areas will have the lighting system installed for this study, as these are where we anticipate participants will spend most of their time

We used this simulation approach to ensure that we could reach our minimum brightness levels. As shown in Fig. 4, we simulated the morning light scene from the L2 condition (6500 K, 280mlux) and the lighting system exceeded our target EML value of 280 mlux in the kitchen and dining areas overlapping where we anticipate a participant sitting. To achieve these EML values, we needed to include two floor lamps with 5-in-1 splitters to increase the amount of light emitted from each lamp (e.g., output from five Philips Hue dynamic light bulbs instead of one).

**Fig. 4 Fig4:**
[figure not shown]
Results from the 3D simulation of the EML values in four different directions. The lights were simulated at the L2 morning condition (6500 K, 280mlux) to determine where in the room participants would experience greater than 280mlux. Heatmaps overlaying the floorplan from Fig. 3 indicate that the sitting area in both the kitchen and dining area will have sufficient light to reach our target brightness levels

For the L3 condition, the morning EML values (500mlux) are increased even further to determine if there is a saturation effect of how much light exposure one needs to also achieve any health-related benefits. The tabletop lamp was not included in Fig. 4 because it was not a part of the L2 condition, however, we were able to use simulations to determine how much additional light would be needed. Based on these simulations, an additional modified tabletop lamp placed in the corner of the kitchen with a light bulb capable of emitting 12,000 lumens at 6500 K would reach the target EML level. Overall, these simulations confirmed we will have sufficient lighting with the designed lighting configuration to achieve our target EML and CCT levels for each lighting condition.

For each room in the main study, we will continue to take measurements using the research grade spectrometer (CL-500 A; Konica Minolta, Inc; Tokyo, Japan) as well as using Blue Iris Fixed Sensors (Blue Iris Lab, California, US) to monitor how ambient light changes each day and across each room. The Blue Iris sensors allow for measuring EML and CCT continuously and will be placed strategically in each room, so we are able to characterize how different floorplans or changes in daylight affect the lighting conditions throughout the study. Additionally, participants will wear the LYS sensor (LYS Technologies LTD™; Copenhagen, Denmark) throughout the time they are awake and moving in the room to capture how much light they are exposed to throughout the study. Both the Blue Iris and LYS sensors will be calibrated in the lab using regression methods similar to those described by Bäumker et al. prior to the start of the study [94]. Although there are different types of floorplans in the facilities where this study will be conducted, the electrical configurations are expected to be similar among all the residences. Using both the wearable and static light sensors and simulating as described, we expect to be able to successfully determine how exposure to different indoor lighting conditions affects the different measures of brain health.

### Statistical analysis plan

Using data from both wearable devices and surveys, the primary comparison will be within-person change in sleep quality scores between each of the three lighting conditions (L1, L2, L3) and the same scores measured during the baseline period. The L1 condition serves as an active control condition as this is the same lighting as they would typically experience in the baseline condition. The secondary comparison will be to compare changes in physical activity, heart rate, and survey data across each lighting condition pair. Data collected during the baseline period will also be compared against the L1 condition to determine whether asking participants to change their behavior with the lights (e.g., do not turn the lights off) affects any of the dependent variables of interest, thereby ensuring that any health benefits seen in the dynamic conditions relative to the static condition are likely reflective of improvements over participants lighting as usual. Participants who are eligible only because their partner is eligible will be analyzed separately.

We will use generalized estimating equations to account for the longitudinal repeated-measures design and handle missing data. For the surveys and cognitive assessments, there will be a minimum of 8 measurements per lighting condition (two cognitive assessments per week for four weeks). If only 35 participants are enrolled, we expect 80% power to detect a difference of minimum of 0.45 standard deviations. Conversely, if we have 70 participants enrolled (i.e., all the rooms are double occupancy with both persons eligible) we expect 80% power to detect a minimum difference of 0.3 standard deviations. For either of these scenarios, we expect to be able to detect at least 0.3 standard deviations, yielding sufficient power, even for the relatively infrequent cognitive assessments. To minimize missing data,, we will monitor key metrics (such as response rates) throughout the study using IRB-approved approaches to encourage participation. As a rule of thumb, participants who complete the study with greater than 50% missing data on any outcome measure will not be included in the relevant final analysis population.

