**Discussion:**

We hypothesize participants will have better sleep quality and greater physical activity during the dynamic lighting compared to the static lighting condition. Additionally, we hypothesize there is a maximal threshold at which health-outcomes improve based on light exposure. Study findings may identify optimal indoor lighting solutions to promote healthy aging for older adults.

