### Study design: cross-over study design with an exploratory third condition

The present study employs a two-arm, randomized, cross-over, single-site trial design. Participants will experience three 4-week lighting conditions (indicated as L1, L2, and L3 and described in the “Environmental Lighting Conditions” section to follow and depicted in Fig. 1). Cohort 1 will experience L1 followed by the L2 condition and cohort 2 will experience L2 followed by the L1 condition. Both cohorts will then experience the L3 condition. The primary outcome of this study is to determine how each lighting condition affects measures of sleep quality as assessed using wearable devices and self-report surveys. The secondary outcomes of this study are to determine how each lighting condition affects physical activity, cognitive function, social engagement, and mood as assessed using wearable devices, cognitive tasks, and self-report surveys. We will compare each of these measures between the L1 and L2 condition to test our central hypothesis that exposure to dynamic lighting (L2) will result in improvements of each measure compared to static lighting (L1). We will then compare these measures between L2 and L3 conditions to test our secondary hypothesis that improvements in measures of brain health saturate based on the amount of equivalent melanopic lux (EML) exposure.

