**Fig. 1 Fig1:**
[figure not shown]
Schematic of the cross-over study design. Interested individuals will first perform an eligibility assessment to determine whether they can be consented into the study. Once 35 residences have been recruited (between 35 and 70 participants), participants will be randomized into two cohorts and experience three lighting conditions (L1, L2, L3). Lighting conditions are described in more detail in the “Environmental Lighting Conditions” section

Before starting the first lighting condition (L1 or L2 depending on the cohort), a baseline period lasting approximately 2 weeks will be used to characterize the lighting quality of each participants residence. The lighting in the baseline period will be set to match as closely as possible the lighting that was previously installed. Throughout the baseline, participants will be instructed to use the light as they normally would.

The L1 lighting condition and the baseline condition will have the same lighting parameters and will be configured to match the residents existing lighting prior to installing the current lighting system. Participants will be instructed to keep the lights all the time while awake during the duration of the study, however we gave individuals flexibility to wake up when they naturally did to not disrupt their sleep patterns by shifting to a rigid wakeup schedule.

After each 4-week lighting condition of the cross-over design, participants will experience a 1-week “washout” period during which they will experience the same lighting as the baseline period (L1 condition). After completing the cross-over and subsequent washout period, participants will experience the L3 condition to determine if there is a saturation effect of how much morning blue-rich light is needed to affect the health-related measures of interest.

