## Discussion

We are presenting a novel research protocol to assess how indoor lighting affects several measures of brain health in older adults living in independent living residences. Preservation of brain health is an important component in maintaining function and independence. Many studies of the health benefits of different lighting conditions have focused on individuals who have already developed dementia in assisted living facilities. Our focus here is to understand how similar lighting interventions might be effective at promoting different measures of brain health which have been shown to help mitigate health-risks before the onset of dementia may occur [24]. Understanding how indoor lighting might affect or even improve multiple measures of brain health, such as sleep, physical activity, social engagement, and mood could have significant implications for guiding older adults to maintain their health and well-being as they age.

The design of this study also provides an innovative approach to providing a control to compare against for each condition. The L1 (static lighting) condition will be designed to match as closely as possible the lights that participants initially had installed. However, participants will need to change their behavior during each of the lighting conditions (L1, L2, L3), making the L1 condition an active control condition. Activity recorded during the baseline period during which participants can turn on/off their lights as needed will also be compared with activity recorded during each of the lighting conditions to determine how much of an effect exists during the active control (L1) condition.

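### The stated primary comparison sets each lighting condition against a non-randomised, always-first baseline, not the randomised L2 versus L1 contrast that tests the central hypothesis

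*Protocol article*

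**What the plan says.** The Statistical analysis plan section states that "the primary comparison will be within-person change in sleep quality scores", taken "between each of the three lighting conditions (L1, L2, L3) and the same scores measured during the baseline period". Its secondary comparison covers pairs of lighting conditions, but for physical activity, heart rate and survey data; device-measured sleep is not named there.

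The Study design section says: "We will compare each of these measures between the L1 and L2 condition to test our central hypothesis". The abstract's hypothesis is likewise "better sleep quality and greater physical activity during the dynamic lighting compared to the static lighting condition". The randomised element is order: "Cohort 1 will experience L1 followed by the L2 condition and cohort 2 will experience L2 followed by the L1 condition". Both cohorts then receive L3 last.

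On the baseline period, the text under Figure 1 in the Study design section says: "Throughout the baseline, participants will be instructed to use the light as they normally would". That period lasts about 2 weeks, precedes everything else, and uses the same light settings as L1. The Discussion adds that "participants will need to change their behavior during each of the lighting conditions (L1, L2, L3".

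The analysis section also plans an L1 versus baseline comparison to look for an effect of the changed light use, "thereby ensuring that any health benefits seen in the dynamic conditions relative to the static condition are likely reflective of improvements" over usual lighting.

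**The concern.** The article ties its hypothesis to one contrast and gives the label of primary comparison to another. The labelled one does not use the randomisation. Baseline differs from every condition in position, in length and in the instruction on light use, so anything that shifts sleep between baseline and the later weeks (the lights-on instruction, getting used to the watch and mattress sensor, season) enters every primary contrast as if it were a lighting effect.

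L1 shows the problem most clearly. Its programmed settings equal those of baseline, so one of the three primary contrasts contains no difference in light settings. The analysis section itself uses that contrast to detect a non-lighting effect. At stake is a positive primary result when dynamic lighting does nothing, and a primary result that disagrees with the test of the central hypothesis on the same data.

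**Working it through.** **The plan's own figures.** The analysis section gives 80% power for 0.45 SD with 35 participants and 0.3 SD with 70, without naming the contrast, the alpha, the sidedness or the SD used.

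- For a paired contrast at two-sided 5%, in units of the SD of the within-person difference, the detectable difference is (1.960 + 0.842)/√n. This is 0.474 at n = 35 and 0.335 at n = 70 (0.487 and 0.340 by t-test).
- If SD means the between-person SD and the within-person correlation is assumed to be 0.59, the SD of the difference is √(2 × 0.41) = 0.906 SD. Power at the stated effects is then 0.815 and 0.780.

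The figures are thus reachable with unstated inputs and are not called wrong here. They do not show which contrast was powered.

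**What each contrast estimates.** Let τ be the effect of dynamic over static lighting, b the effect of the changed light use (common to L1 and L2), and g the effect of time since baseline.

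- L2 − baseline = τ + b + g
- L1 − baseline = b + g
- L2 − L1 = τ, once periods are balanced or adjusted for

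L3 − baseline contains b and g as well, with g at its largest because L3 is always last.

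**Size of the error when τ = 0.** The article gives no value for b or g, so a common shift δ is assumed, in units of the SD of the within-person change. The test is a two-sided 5% one-sample t-test with non-centrality δ√n, treating participants as independent.

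| δ | n | δ√n | Chance of a significant change from baseline |
|---|---|---|---|
| 0.1 | 35 | 0.592 | 9% |
| 0.1 | 70 | 0.837 | 13% |
| 0.2 | 35 | 1.183 | 21% |
| 0.2 | 70 | 1.673 | 38% |
| 0.3 | 35 | 1.775 | 41% |
| 0.3 | 70 | 2.510 | 70% |

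The rows for 0.1 come from simulation (20,000 trials per scenario) and the others from the non-central t distribution. Simulation agrees with the latter to within about one percentage point.

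Further simulated cases with τ = 0:

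- Drift of 0.1 per period and b = 0: L2 versus baseline is significant in 14% (n = 35) and 24% (n = 70) of trials.
- Drift of 0.1 per period and b = 0.2: 52% and 82%.
- L1 versus baseline rejects at essentially the same rates throughout.
- The period-adjusted L2 − L1 contrast has bias 0.00 and rejects in 4.8% to 5.2% of trials in every scenario.

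**Precision.** If night-to-night noise dominates and nights are independent, 14 baseline nights against 28 condition nights give a standard error ratio, relative to L2 − L1, of √[(1/28 + 1/14)/(2/28)] = √1.5 = 1.22. The baseline contrast would then be about 22% less precise. If the SD of the difference is the same for both contrasts, they have equal power.

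**The case against.** The strongest reply is that the randomised contrast is already planned. The Study design section commits to L2 versus L1 for every measure, and the pairwise secondary comparison includes survey data, hence the sleep surveys. That is true: the fault lies in which contrast is called primary, not in a missing analysis. But the label decides what the trial may claim, and the analysis section does not name an L2 versus L1 comparison of device-measured sleep.

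A second reply is that change from baseline was meant to be compared between conditions, with L1 as active control. Since (L2 − baseline) − (L1 − baseline) = L2 − L1, that would recover the right contrast. The sentence does not say so; it sets each condition against baseline. A fuller analysis plan may say it, but this is an explicit statement in the article, not a detail left out.

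Third, the L1 versus baseline check does bear on the instruction effect, and the article hedges its inference as likely. The check is informative, but it estimates instruction and time together. In cohort 2, L1 also follows L2, although a 1-week washout lies between them. It cannot carry the assurance placed on it.

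Three limits stand. The shift sizes are assumed, and at 0.1 SD the inflation is modest. Practice effects concern the cognitive tasks more than sleep. The Study design section does not itself call L2 versus L1 primary, so the conflict is between a hypothesis test and a labelled comparison, not between two declared primary analyses.

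**Conclusion.** The concern holds. As written, the primary comparison does not use the randomisation, cannot separate dynamic lighting from the lights-on instruction and time, and differs from the contrast that tests the central hypothesis. This follows from the design and needs no assumed number.

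The size does rest on assumptions. Common shifts of 0.1 to 0.3 SD of the within-person change give false-positive rates of 9% to 41% with 35 participants and 13% to 70% with 70, against a nominal 5%, for independent participants and two-sided 5% tests. The 22% loss of precision applies only if independent night-to-night noise dominates and the baseline gives 14 usable nights. The point should be corrected before the data are analysed.

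**What to change.** In the Statistical analysis plan section:

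- Name the within-person L2 minus L1 difference in sleep quality from the two-period cross-over, device-measured sleep included, as the primary comparison, with period and sequence in the model.
- Use baseline values as a covariate or descriptively. Label the L1 and L2 contrasts with baseline as secondary and non-randomised, and all L3 contrasts as exploratory, since L3 is always last.
- Report L1 minus baseline as an estimate with a confidence interval, and drop the claim that it ensures anything about the dynamic conditions.
- State which contrast the power figures refer to.

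This is rewording and needs no new data. The baseline contrasts lose primary status. For the same SD of the within-person difference, the change costs no power.

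### The baseline-versus-L1 check is stated without regard to cohort, but in cohort 2 L1 comes after L2, so the check cannot by itself ensure that gains over L1 are gains over usual lighting

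*Protocol article*

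**What the plan says.** The Statistical analysis plan section states: "Data collected during the baseline period will also be compared against the L1 condition". The purpose is "to determine whether asking participants to change their behavior with the lights (e.g., do not turn the lights off) affects any of the dependent variables". The same sentence then draws a conclusion, "thereby ensuring that any health benefits seen in the dynamic conditions relative to the static condition", to the effect that these benefits likely reflect a gain over the participants' usual lighting. The Discussion returns to the comparison, for activity, as a way "to determine how much of an effect exists during the active control (L1) condition". Neither place names a cohort or a period.

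The logic rests on a statement in the text under Fig. 1: "The L1 lighting condition and the baseline condition will have the same lighting parameters". At baseline, participants use the lights as they normally would; in L1 they are asked to keep them on while awake.

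The order of conditions differs by cohort: "Cohort 1 will experience L1 followed by the L2 condition and cohort 2 will experience L2 followed by the L1 condition".

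**The concern.** The check is meant to isolate one thing, the instruction to keep the lights on. In cohort 1 that instruction is the only planned change between baseline and L1. In cohort 2, participants have also had four weeks of L2 and a washout week before L1 begins. Baseline-versus-L1 in that cohort can therefore also contain residual L2 effect and five further weeks of practice, season or device fatigue.

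What is at stake is the interpretation of the control. If keeping the lights on worsens outcomes, part of any L2 gain over L1 is recovery from a poor control and not a gain over usual lighting. The protocol's hypothesis is that L2 improves every measure, and the cognitive tasks are repeated twice a week. Residual benefit and practice gains would both lift cohort 2's L1 scores and could hide such a worsening. With other signs, the same mechanism would produce an apparent lights-on effect where there is none.

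**Working it through.** **Timeline.** Inputs: "a baseline period lasting approximately 2 weeks will be used"; "Participants will experience three 4-week lighting conditions"; and a one-week washout after each cross-over condition (text under Fig. 1). Sum: 2 + 4 + 1 + 4 + 1 + 4 = 16 weeks, which reproduces the duration in the Abstract. L1 is in weeks 3-6 in cohort 1 and weeks 8-11 in cohort 2. Midpoints are at 1 week (baseline), 4 weeks (cohort 1 L1) and 9 weeks (cohort 2 L1). The gaps from baseline are 3 and 8 weeks, a difference of 5 and a mean of 5.5.

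**What each contrast estimates.** Let b be the lights-on effect, c the average L2 carry-over into cohort 2's L1, and d a linear drift per week.
- Cohort 1: b + 3d
- Cohort 2: b + c + 8d
- Pooled, equal cohorts: b + c/2 + 5.5d
- Cohort 2 minus cohort 1: c + 5d

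**Size (assumed c and d; the document gives neither).** Take an L2 effect of 0.30 to 0.45 SD (the protocol's detectable differences), 10-20% of it persisting on average, and d from 0 to 0.02 SD per week.
- Low end: c = 0.1 × 0.30 = 0.03 and d = 0. Cohort 2 is shifted by 0.03 relative to cohort 1, and the pooled estimate by 0.015.
- High end: c = 0.2 × 0.45 = 0.09 and d = 0.02. Cohort 2 is shifted by 0.09 + 5 × 0.02 = 0.19, and the pooled estimate by 0.095.
- High end, counting drift common to both cohorts: pooled shift 0.045 + 5.5 × 0.02 = 0.155; cohort 1 shift 3 × 0.02 = 0.06.
- With c = d = 0 the bias is zero. With b = 0 and the high-end values, the pooled check shows +0.155 SD where the instruction does nothing.

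**Power.** The protocol gives 80% power at 0.45 SD (N = 35) or 0.30 SD (N = 70), without alpha, sidedness or correlation. I scale from those figures with a two-sided 0.05 test: power = Φ(2.80 × |estimate| / MDE − 1.96), where MDE is the protocol's detectable difference, and 2.80 is divided by √2 for one cohort. This assumes that baseline-versus-L1 is as precise as the planned contrasts, which is generous because baseline is half as long as a condition. The true b is set to the detectable worsening.

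| N, b | c, d | Pooled estimate | Power | Cohort 1 estimate | Power |
|---|---|---|---|---|---|
| 35, −0.45 | 0, 0 | −0.45 | 80% | −0.45 | 51% |
| 35, −0.45 | 0.03, 0 | −0.435 | 77% | −0.45 | 51% |
| 35, −0.45 | 0.09, 0.02 | −0.295 | 45% | −0.39 | 40% |
| 70, −0.30 | 0, 0 | −0.30 | 80% | −0.30 | 51% |
| 70, −0.30 | 0.03, 0 | −0.285 | 76% | −0.30 | 51% |
| 70, −0.30 | 0.09, 0.02 | −0.145 | 27% | −0.24 | 35% |

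A harsher case, N = 70 with c = 0.075 and d = 0.03, gives a pooled estimate of −0.30 + 0.0375 + 0.165 = −0.0975 (power 15%) and a cohort 1 estimate of −0.30 + 0.09 = −0.21 (power 28%).

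**How sharp a by-cohort comparison is.** The pooled standard error is MDE/2.80, or 0.161 (N = 35) and 0.107 (N = 70). A single cohort's is √2 ≈ 1.4 times larger, and that of the difference between cohorts is twice the pooled one. The 95% half-widths are about 0.32 and 0.21 pooled, 0.45 and 0.30 for one cohort, and 0.63 and 0.42 for the difference. A high-end difference of 0.19 SD lies well inside the last of these.

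**The case against.** Several objections carry weight.

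- **Pooling is not stated.** A reader might infer that the plan averages the cohorts and ignores sequence. The text says neither; it names generalized estimating equations without listing terms, and a fuller plan could add them. That stands. What remains is the unqualified comparison and the assurance drawn from it. A period term would help only in part. It could absorb the extra five weeks in cohort 2 if there is no carry-over, but baseline always comes first, so it cannot separate the lights-on effect from the time elapsed since baseline.
- **Carry-over is only possible.** The washout is there to remove it. Under exponential decay (an assumption), 10-20% persisting on average over weeks 1 to 5 after L2 ends means that 39-54% of the effect is still present when the washout ends. Nothing in the document supports or excludes that.
- **The direction is open.** A reader might infer that the check falsely reassures. That needs a harmful lights-on effect together with upward carry-over or drift. Season and fatigue can push down, and the instruction might help.
- **The consequence is easily overstated.** If L2 beats L1 by 0.45 SD and lights-on costs 0.10 SD, L2 still beats usual lighting by 0.35 SD. A 0.10 SD worsening would be detected with only about 10% (N = 35) or 15% (N = 70) power even without bias. The sleep analysis also sets every condition directly against baseline, though that contrast is exposed to time as well.
- **Cohort 1 alone is no cure.** It keeps 3 weeks of drift. Counting only the shift that cohort 2 adds (0.015 to 0.095), the pooled check has 60-77% power at N = 35 and 48-76% at N = 70, against about 51% for cohort 1 without drift.

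The last two points rule out claiming that an artefact would be accepted as benefit, or that the conclusion should move to cohort 1. They do not restore the assurance, because the pooled figure is still a mixture.

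**Conclusion.** The point holds as a limit on what this check can conclude. Baseline-versus-L1 measures different things in the two cohorts, the plan does not distinguish them, and it draws a stronger inference than either contrast supports. Under the assumed ranges, cohort 2 shifts the pooled estimate by 0.015 to 0.095 SD relative to cohort 1, or by up to 0.155 SD in total once shared drift is counted. With no carry-over and no drift the shift is zero. These sizes rest on assumed persistence, linear drift and equal cohorts, none of which the document gives.

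The documents do not show that the control is misleading, that L2 effects persist past the washout, or that cohort 1 gives a clean answer. This is a supportive check, and the randomised L2-L1 comparison is unaffected. The change is a cheap improvement to reporting and interpretation.

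**What to change.** In the Statistical analysis plan section:

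1. Report baseline-versus-L1 by cohort, with confidence intervals, alongside the pooled estimate.
2. Present the difference between cohorts as a check on carry-over and drift, and describe cohort 1 as the estimate free of L2 carry-over but not of drift.
3. Replace the claim that the comparison ensures the interpretation with a conditional one: gains over L1 are read as gains over usual lighting only if the cohorts agree and the intervals exclude a worsening that the sponsor has named in advance as relevant.
4. State that a non-significant cohort 1 result is not enough, since its power at the protocol's detectable effect is about 51%.

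The cost is a few sentences, with no new data and no loss of the pooled estimate. The downside is precision: cohort-specific standard errors are about 1.4 times larger, so agreement between cohorts is only a weak test and the honest conclusion may be that the question stays open.
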